### Hypotheses

Main effects: Control, Intervention A (instruction), Intervention B (instruction plus reward), and Intervention C (instruction plus reward and instruction in post-intervention phase) groups

H1: Feedback display will increase handwashing activity in the kindergarten (in the short term) during intervention phase
For intervention A, B, and C groupsFor intervention B and C groups more than intervention A groupH2: Handwashing activity in the kindergartens will decline with time (while the display will still be turned on)
For intervention A group less than intervention B and C groups during the beginning of the post-intervention phaseFor intervention B group less than intervention C group during post-intervention phase.For control group less than intervention A, B, and C groups in all phases.Motivation crowding out: Measurement-basedH3a: Effect will partially persist, when feedback display in kindergarten will be turned off during the beginning of post-intervention phase. For intervention C groups less than intervention A and B groups. (Explanation: habit will be formed, there will be partial motivation crowding out, impact in increased self-efficacy will be stronger)H3b: Effect will vanish and handwashing will return to baseline behaviour for intervention B group in post-intervention phase. (Possible explanation: no habit will be formed, there will be no motivation crowding out)H3c: Effect will vanish and handwashing activity will drop below baseline behaviour for intervention A group in post-intervention phase. (Possible explanation: there will be crowding out)
Acquisition of competences and self-efficacy: Intervention A, B, and C groupsH4a: Feedback intervention will increase competences and self-efficacy level of children after the intervention phase–for intervention B and C groups stronger than for intervention A groupH4b: Feedback intervention will increase competences and self-efficacy level of children after post-intervention phase–for intervention C group stronger than for intervention B group and for intervention B group stronger than for intervention A group.

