**Fig 1 pone.0280686.g001:**
[figure not shown]
Schedule of enrolment, intervention, and assessments.

This study will be a four-arm cluster randomized controlled trial study with three phases and a twelve-month follow-up by country stratification. This study will evaluate the effectiveness of the gamified live feedback intervention on children’s handwashing behaviour, self-efficacy, and motivation in three different phases: the baseline, intervention, and post-intervention phases. In Finland, there will be a twelve-month follow-up after the baseline phase. This study will consist of four groups, the control group, and three different intervention groups. All the groups will have automated monitoring systems installed before the start of the baseline phase and will be available in all phases. The system will be de-installed after the post-intervention phase.

During the baseline phase, all the groups will have no screen activity. During the intervention phase, the control group will have no screen activity. The intervention A group will have a screen display providing handwashing instructions but no reward, and the intervention B and C groups will receive handwashing instructions and rewards from the screen display. During the post-intervention phase, all the groups will have no screen activity except the intervention C group which will receive handwashing instructions but no reward (Fig 2).

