### Data analyses

Data will be analysed using qualitative and statistical methods. All eligible participants will be included in the analysis. The statistical analyses will be performed with R. The categorical and numerical data will be analysed using one-way analysis of variance (ANOVA). Qualitative analysis will be presented thematically [42].

For the measurement data from the system:

Data pre-processing: Data will be investigated where water and soaping data are combined to single handwashing procedures. Data points that are not valid (outside of kindergarten opening hours) will be removed. The descriptive statistics of the clusters, randomization checks, ICC (intracluster correlation) will be calculated. The data will be analyzed using linear fixed-effect regression model for panel data, and dependent variable soaping time. The four groups will be compared in baseline, intervention, and post-intervention phases.

For the survey and staff interview data:

The comparison among the groups will be implemented using random effects regression, allowing for the clustered nature of the data, and adjusted using the covariates of the adjusted analyses (when a small number of clusters are present) [43]. Simple bias analysis will be used to quantify the uncertainty of the biases such as confounding variables [33]. The qualitative results of the survey and kindergarten staff interview will be analysed and compared thematically. The four groups will be compared after intervention phase.

For the children interview and observation data:

The analyses will be compared among groups based on the complete data only. The comparative analyses approach used to calculate the observation, survey, and staff interview will be used. The self-efficacy measurement scale will be developed and evaluated for its psychometric properties [44,45]. The qualitative result of the observation and interviews will be analysed and compared thematically [42]. Children who will participate the interview at one time point will be considered as missing data, these will be excluded from the analysis. The four groups will be compared in baseline, intervention, and post-intervention phases.

For the sickness day data:

The total sick leave days are compared among the groups one year before and after the start of the baseline phase.

The statisticians of the two universities will validate the statistical results of the data.

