### Limitations

The intervention, technology and experimental setup were evaluated in a pre-study. The pre-study showed promising results with regards to main effects: a statistically significant increase in handwashing time was observed in the treatment kindergarten. Minor issues and challenges that were encountered in the pre-study are considered and improved in the presented study here diminish existing limitations. Especially the technical hardware was improved to diminish the risk of hardware failures and outages. Furthermore, a research member is assigned to address the technical issues during the study immediately, if any issues happen. A possible limitation is the Hawthorne effect when observing the handwashing activity, as individuals might change their behaviour when knowing that they are being observed. To manage this, the observers will not be informed the participants when and where the observation sessions take place, and during the observations, they will be informed that the focus is on hand hygiene in general. Another limitation is the ongoing Covid-19 pandemic, as it can affect the collection of sick leave days for the children and kindergarten staff. To minimize this, sick leave data one year before the baseline phase will be obtained from the record of the kindergarten. Covid-19 also affect the children’s hand hygiene behaviour and performance. Thus, there will be four different groups to be compared in three timepoints and a 12-month follow-up.

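### H3b and H3c, as worded, measure a vanished effect and crowding out against the arm's own baseline and are not tied to the concurrent control arm

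*Protocol article*

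**What the plan says.** Under Hypotheses, the prediction for intervention B is "H3b: Effect will vanish and handwashing will return to baseline behaviour for intervention B group in post-intervention phase". For intervention A it is "H3c: Effect will vanish and handwashing activity will drop below baseline behaviour for intervention A group in post-intervention phase". The two carry opposite readings. A return to baseline in arm B goes with no crowding out; for a fall below baseline in arm A the article adds "Possible explanation: there will be crowding out". The control arm appears in neither, but it does appear in H2: "For control group less than intervention A, B, and C groups in all phases".

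The control arm is observed throughout. The trial design text says "All the groups will have automated monitoring systems installed before the start of the baseline phase and will be available in all phases". For the sensor data, Data analyses plans a linear fixed-effect panel regression of soaping time and adds "The four groups will be compared in baseline, intervention, and post-intervention phases". It does not say whether the model contains phase effects or group-by-phase terms, or which contrast decides H3b or H3c.

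Two statements bear on how stable the baseline is. Limitations says "Covid-19 also affect the children’s hand hygiene behaviour and performance", and its next sentence gives the comparison of four groups over time as the response. Implementation places a teaching session for all children in the middle of the three-week baseline.

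**The concern.** Whether crowding out happens is part of the stated objective. The dividing line between the two readings is the arm's own level six weeks earlier: baseline covers weeks 1 to 3 and post-intervention weeks 7 to 9. Anything that moves handwashing in every kindergarten over that time moves an arm relative to the line without involving the display.

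A shared fall could come from changing Covid-19 habits or from fading of the mid-baseline lesson. It would push an arm with no crowding out below its baseline, and would make a lasting gain look as if it had vanished. A shared rise would do the reverse and mask a true loss of motivation. The control arm is there to separate these cases, and the two hypotheses do not use it.

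**Working it through.** **No stated figure to reproduce.** The article gives no number for this point. The sample size (31 × 3.418 = 105.96, so 106) does not enter it.

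**Why the two yardsticks differ.** Let g be the true carry-over effect in an arm and t the drift common to all arms, both in SD of the outcome. The arm's own change is g + t. The arm's change minus the control arm's change is (g + t) − t = g.

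- g = 0, t = −0.1: own change −0.1 (reads as crowding out); control-adjusted 0.
- g = +0.1, t = −0.1: own change 0 (reads as effect vanished); control-adjusted +0.1.
- g = −0.1, t = +0.1: own change 0 (reads as no crowding out); control-adjusted −0.1.

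**Inputs for the size.**
- Upper bound on information: the pre-study in Sample size recorded 10,000 events over 42 days in four clusters, so 10,000 / 4 / 42 × 21 = 1,250 events per cluster per 21-day phase.
- Lower value: 40, the planned number of children per kindergarten. Events from the same children on the same days are correlated, so the effective sample lies below 1,250.
- Drift d (downward, in SD): assumed 0 to 0.2. The article gives neither the SD of soaping time nor any drift.

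**Formula.** With effective n per arm and phase, SE = √(2/n). The chance of declaring the arm below its own baseline when there is no true effect (lower tail 0.025) is Φ(d/SE − 1.96).

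| Effective n | SE | d = 0 | d = 0.05 | d = 0.10 | d = 0.20 |
|---|---|---|---|---|---|
| 40 | 0.224 | 2.5% | 4.1% | 6.5% | 14.3% |
| 100 | 0.141 | 2.5% | 5.4% | 10.5% | 29.3% |
| 250 | 0.089 | 2.5% | 8.1% | 20.0% | 60.9% |
| 1,250 | 0.040 | 2.5% | 23.9% | 70.5% | 99.9% |

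Worked cell: n = 250, d = 0.10 gives 0.10/0.0894 − 1.96 = −0.84, and Φ(−0.84) = 0.20.

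**Same test on the control-adjusted change.** If the drift is common, d cancels and the rate stays at 2.5% in every cell. The SE becomes √(4/n), which is √2 = 1.41 times as large.

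**What the adjustment does not remove.** Suppose each kindergarten also has its own drift with SD 0.05 (assumed), one kindergarten per arm, n = 1,250. The difference then has true SD √(2 × 0.05² + 4/1,250) = √0.0082 = 0.0906. A test that counts only event-level error uses the limit 1.96 × 0.0566 = 0.111. The false rate is Φ(−0.111/0.0906) = Φ(−1.22), about 11% against a nominal 2.5%.

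**The case against.** The strongest reply is that the hypotheses are predictions, not test rules. The only stated sensor analysis compares all four groups in all three phases with a panel model. If that model has phase effects and group-by-phase terms, it yields the control-adjusted contrast directly. Such detail is commonly left to an analysis plan, and none is shown. Limitations also names the Covid-19 influence and points to the four-group comparison as its answer. The crowding-out readings are offered only as possible explanations, and the word effect could itself be taken as relative to control.

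Much of this stands, and it rules out stronger readings that a reader might infer:

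- That H3b and H3c will in fact be judged without the control arm. The article does not say so; it names no deciding contrast at all.
- That the protocol itself predicts a decline in the control arm. H2 reads "Handwashing activity in the kindergartens will decline with time (while the display will still be turned on", and the control arm never has a display. Its control clause may mean a smaller decline or a lower level, so it cannot carry that claim.
- That a false finding is close to certain. The high rates in the table need all 1,250 events to be independent and a drift that is only assumed.

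The reply does not remove the mismatch. Comparing groups within each phase is not the same as testing a change from baseline against the control arm's change. The hypotheses state a within-arm yardstick, and nothing links them to the model. An analyst could follow either one and could choose after seeing the data.

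**Conclusion.** The point holds as a mismatch between the wording of H3b and H3c and the controlled comparison that the design makes possible. Taken literally, H3c is met by any sufficient decline shared with the control arm, and H3b can be met by a real gain offset by such a decline. The direction is certain; the size is not. For a common fall of 0.1 SD, the false rate rises from 2.5% to about 7% with an effective n of 40 and to about 70% with 1,250. This rests on a normal approximation, no true carry-over effect, and drift and effective sample sizes that are assumed. It does not show that the planned panel model is wrong, only that it is not tied to these two hypotheses. It should be settled before the post-intervention data are analysed, because the crowding-out conclusion turns on it.

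**What to change.** Restate H3b and H3c as the arm's change from baseline to post-intervention minus the control arm's change over the same phases. In Data analyses, name this group-by-phase contrast of the panel model as the one that decides them:

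- H3c (arm A): the contrast is below zero.
- H3b (arm B): the contrast lies within a margin of zero stated in advance. A return to baseline is a claim of no difference, and a non-significant test does not establish it.

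Report each arm's raw change from its own baseline descriptively.

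The cost is the wording of two hypotheses, one named contrast and one margin. No new data are needed, since the control arm is monitored in all phases. The interval widens, by a factor of about 1.41 if the arms contribute equal information. The change removes only drift common to the arms. Sample size plans three kindergartens for four groups, with two intervention groups covered by one cluster, so there is about one kindergarten per arm. Drift specific to a kindergarten then stays confounded with the arm effect, and the article should say so as a limitation.

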### Trial design

In this article, we describe a clinical protocol for a study using a cluster randomized controlled trial following the Standard Protocol Items: Recommended for Interventional Trials (SPIRIT) guidelines [31] (S1 Table). The study design follows the CONSORT guidelines for cluster Randomized Controlled Trials [32]. The SPIRIT schedule enrolment is reported in Fig 1.

**Fig 1 pone.0280686.g001:**
[figure not shown]
Schedule of enrolment, intervention, and assessments.

This study will be a four-arm cluster randomized controlled trial study with three phases and a twelve-month follow-up by country stratification. This study will evaluate the effectiveness of the gamified live feedback intervention on children’s handwashing behaviour, self-efficacy, and motivation in three different phases: the baseline, intervention, and post-intervention phases. In Finland, there will be a twelve-month follow-up after the baseline phase. This study will consist of four groups, the control group, and three different intervention groups. All the groups will have automated monitoring systems installed before the start of the baseline phase and will be available in all phases. The system will be de-installed after the post-intervention phase.

During the baseline phase, all the groups will have no screen activity. During the intervention phase, the control group will have no screen activity. The intervention A group will have a screen display providing handwashing instructions but no reward, and the intervention B and C groups will receive handwashing instructions and rewards from the screen display. During the post-intervention phase, all the groups will have no screen activity except the intervention C group which will receive handwashing instructions but no reward (Fig 2).

**Fig 2 pone.0280686.g002:**
[figure not shown]
The design and data collection of the study.

The design of this study is cluster randomized controlled, where one kindergarten serves as one cluster. Clustering will be used since the hand hygiene intervention is designed to be installed in certain areas to be used in groups. Kindergartens will be assigned as clusters rather than individuals to minimize the potential contamination among the groups, and to more accurately follow the process that will be taken at scale [33,34].

### Theoretical framework

This study will use Albert Bandura’s Social Cognitive Theory (SCT) as the theoretical framework. According to this theory, the three factors: personal, environmental, and behavioural determine human behaviour and are mutually interacting among each other [18]. In this conceptual model, the human agency is functioning within the interactional causal structure to obtain and maintain a behaviour (Fig 3).

**Fig 3 pone.0280686.g003:**
[figure not shown]
Illustration of the reciprocity of the factors determining hand hygiene behavior.

The reciprocal causation, action, cognitive, and other personal and environmental factors function as interacting determinants. This model states that individuals are not autonomous agents, but they are making a causal contribution to their motivation and action within the triadic reciprocal causation [35]. In addition, motivation is self-regulated by the influence of proactive and feedback mechanisms, but the adaptation of humans will depend on the forethought of feedback control of action [18].

The technology to be used in this study that provides live feedback (instructions and reward) when performing handwashing can build positive outcome expectations, enhance self-efficacy, and attain a goal (Fig 3). This kind of intervention can promote to maintain and improve hand hygiene behaviour by enhancing motivation and self-efficacy. Figs 3 and 4 show how the theory is applied using the live feedback intervention.

**Fig 4 pone.0280686.g004:**
[figure not shown]
The application of the SCT using the live feedback intervention.

### Study setting

This study will be conducted in kindergartens of different locations around Turku, Finland and Bamberg, Germany. In Germany and in Finland, kindergartens are under the supervision of Early Childhood Education and Care (ECEC) [36]. It is a part of Finnish and German education systems which support the children’s development and focus on learning through play. It is an essential stage on the child’s path of growing and learning. ECEC is a systematic and goal-oriented entity that includes upbringing, education, and care, specifically emphasizing pedagogy aiming to promote and support holistic growth, development, health, and wellbeing (Act on Early Childhood and Care). Groups of children in the kindergartens may be formed in various ways, considering the children’s ages or needs for support. Distribution on staffing and maximum group sizes are considered in forming the groups of children. The kindergarten staff are composed of preschool teachers and assistants who are responsible for the daily activities of the children [36–39].

### Eligibility criteria

The kindergartens around Turku, Finland and Bamberg, Germany will be eligible to participate in the study. The criteria for the participants will be A) children enrolled in the kindergartens aged two years and six months to six years old, their parents or legal guardians, and kindergarten staff who will provide observational measures; B) give informed consent by both the child (verbal consent) and parents/legal guardians and kindergarten staff; C) can understand and communicate Finnish or German. The exclusion criteria will be participants that cannot answer the assessment data.

### Outcome measures

The primary outcome is the hand hygiene behaviour of the children. The system will measure the hand hygiene activities which includes the start time of extraction, water volume, water temperature, and end time of extraction; from these data, the following data will be derived: average flow rates, approximation of energy consumption, quality and duration of handwashing, and time stamp of soap used.

The secondary outcomes are self-efficacy, intrinsic motivation, hand hygiene behaviour at home from parents’ survey, hand hygiene behaviour in kindergartens from kindergarten staff, and hand hygiene behaviour in the kindergarten by observation sessions. Self-efficacy and intrinsic motivation will be measured from the children’s one-on-one interview, a three-point Likert scale with open-ended questions. The children will be asked easy and simple questions about their hand hygiene performance, self-regulation on motivation, emotional states, and decisional in performing handwashing. They will respond by pointing their answer from the three smiley faces (sad, neutral, and happy). Colourful smiley faces will be constructed to catch the attention of the children. Each question is followed by open-ended questions to explore their opinions regarding the topic asked and to support their answers. The children interview includes introduction of the interviewer and asking simple questions regarding their day or regular activities for the children to feel comfortable. The parent survey will be an electronic survey composed of five-point Likert and open-ended questions about the observed hand hygiene behaviour of the children at home. The kindergarten staff interview will also include five-point Likert and open-ended questions, evaluating the hand hygiene behaviour of the children in the kindergartens. The assistant researchers will observe the hand hygiene behaviour of the children during the handwashing activity in the kindergartens. Observation sessions will include a checklist consisting of the phases of handwashing, the checklist will follow the hand hygiene guideline of the United Nations Children Fund (UNICEF).

The tertiary outcome is the number of sick leave days of the children and kindergarten staff (applies in Finland) considering the seasonal change.

### Study participants

The population of the study will be the preschool children who are enrolled in kindergartens. The children aged between 2.6 to 6 years old, their parents, or legal guardians, and the kindergarten staff who will be providing the observational measures.

